### 2.3. Sample Size and Statistical Framework

The sample size calculations were based on the primary efficacy outcome, that is, the hierarchical analysis time to of all-cause death, myocardial infarction, stroke, unstable angina, hospitalization for heart failure, urgent coronary revascularization and hospitalization for respiratory infection (excluding COVID-19), using the win ratio methodErro! Fonte de referência não encontrada.. In the win ratio method, every patient from the intervention group will be compared against every patient from the control group. Among each unique patient pair, the “loser” will be the first patient who presents an outcome, according to a predefined hierarchy. For example, if patient X dies and patient Y is alive by the end of follow-up, patient Y will be considered the “winner” in that match. If both participants die during the study, the “winner” will be the participant with the longest time alive since randomization. In case the patients remain tied – if neither dies by the end of 12 months or if both die with the same follow-up time – the next item in the hierarchy, myocardial infarction, will be analyzed in the same

[figure not shown]

manner (presence vs. absence of event and, if both presented the outcome, time to first event). If the patient pair remains tied, the analysis will be proceeded similarly for each component of primary outcome in the hierarchy. A tie will be declared if participants remain tied after the final item, hospitalization for respiratory infection. This will happen if neither patient presents an outcome or if they present the same outcomes for the first time at the same follow-up times. Participants will be censored at the 12-month follow-up; if the follow-up time for any participant is censored before this time due to any reason, comparisons with this individual will be made only until the moment of censorship.

The win ratio method will be analyzed as the following:

H0:  $\Psi=1$  (win ratio = 1): the ratio of all winners in the intervention group by all winners in the control group is equal to 1.

H1:  $\Psi \neq 1$  (win ratio  $\neq 1$ ): the ratio of all winners in the intervention group by all winners in the control group is not 1.

The win ratio statistic is defined as the ratio of wins ( $N_w$ : Number of Wins of the intervention group,  $N_L$ : Number of Losses of the intervention group) in each group (intervention vs. control).

$$\text{Win ratio} = \frac{\sum N_w}{\sum N_L}$$

This result will be presented with the accompanying 95% confidence interval. The p-value will be obtained by the following formula, as described by Pocock et al. (2012):

$$z = (P_w - 0.5) / [P_w * (1 - P_w) / (N_w + N_L)]^{1/2}$$

Where  $N_w$  indicates the number of wins,  $N_L$  indicates the number of losses, and  $P_w$  indicates the proportion of wins:  $P_w = N_w / (N_w + N_L)$ .

Based on the trial's reported aggregate data by the time the second enrollment season ended, we have calculated the sample size considering the following control-group estimated rates based on events-reported (non-adjudicated) at 12 months for the components of the hierarchical endpoints:

[figure not shown]

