In this sense, and based on the results of the aforementioned meta-analysis, non-controllable factors (COVID-19) and the findings of the IAMI trial, we recalculated the VIP-ACS sample size using a statistical Win Ratio (WR) approach, for analysis of efficacy of the double-dose influenza vaccine compared to the standard dose vaccine, in which it was estimated that the inclusion of 1800 patients (900 per group) for a WR of 1.41 with a power of 82.6% and an alpha of 5 %. These data were obtained over 10,000 simulations, considering the following event rates in the control group: death, 7.0%; AMI, 3.4%; stroke, 1.0%; hospitalization for unstable angina, 2.7%; hospitalization for heart failure, 2.9%; emergency revascularization, 1.0% and hospitalization for respiratory infections, 1.0%, and assuming a reduction of these events with double-dose vaccine in: death by 2.0%; AMI by 0.9%; Stroke by 0.3%; Hospitalization for unstable

angina by 0.8%; Hospitalization for heart failure by 0.7%; Emergency coronary revascularization by 0.2% and Hospitalizations for respiratory infections by 0.3%.

Considering that the primary endpoint of the VIP-ACS comprises more individual endpoints than the IAMI trial, and from the meta-analysis studies, the sample size calculation proposed to the VIP-ACS to assess possible reductions in hierarchical events of the primary endpoint is comprehensive and conservative to the purpose of the study, and overcomes the external conditions involved in the COVID-19 pandemic.

The analysis of the primary endpoint will exclude hospitalizations for respiratory causes caused by COVID-19. To this end, a sensitivity analysis and other exploratory analysis of the impact of COVID-19 on VIP-ACS events are planned.

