## 2. STUDY METHODS

### 2.1. Trial Design

A randomized controlled, open-label, multicenter, superiority, parallel group and 1:1 allocation trial, with blind assessment of clinical outcomes.

After evaluation of an acute coronary syndrome (ACS) confirmed by exams, and during hospitalization phase, if the patient attends to the enrollment criteria and signs the consent form, the randomization to one of the vaccination arms of the study will occur.

The patient can be randomized to one of the following arms:

- 1) Double-dose influenza vaccination (DD) – administered during the hospital stay phase, as early as possible following randomization
  - 2) Standard dose influenza vaccination (SD) – administered  $30 \pm 5$  days after randomization
- Subsequently to the randomization date, each patient will be followed for 12 months, for the monitoring of cardiovascular and respiratory events.

The study was planned to initiate the randomizations from the availability of the 2019 influenza vaccine (March 2019) and continue until November 2020, even beyond the national influenza immunization campaign period for those years. Despite the effort made to completion of the planned inclusion sample, ensuring the representativeness of both planned influenza periods, the first recruitment period was impaired due to regulatory delays in the study initiation. Since the beginning of the second recruitment period, the protocol was amended (version 4, of 04-Jul-2020), the study sample size was recalculated as an event-driven study, and the timing of final analysis was set as the date when 953 primary efficacy outcome events would have occurred, even if it was necessary to continue recruitment through the year 2021.

In 2020, the COVID-19 pandemic impacted recruitment and conduct of the trial. First of all, national influenza vaccination campaign was anticipated and the adherence to immunization was higher than before, making fewer patients eligible for the study during this recruitment period. Second, enrollment was hurdled because patients were constrained of returning to study in-person visits to receive the outpatient vaccination, should they have been assigned to the control group. Due to those issues, the study steering committee decided to end recruitment after 1,800

[figure not shown][figure not shown]

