### Expected absolute risk reductions for the components of the primary outcome (representing 28% relative risk reduction)

|                                                                  |      |
|------------------------------------------------------------------|------|
| Death                                                            | 2.0% |
| Myocardial Infarction                                            | 0.9% |
| Stroke                                                           | 0.3% |
| Unstable angina                                                  | 0.8% |
| Hospitalization for heart failure                                | 0.8% |
| Urgent revascularization                                         | 0.2% |
| Hospitalization for respiratory infection
(Excludes COVID-19) | 0.3% |

Sample size and power calculation were based on 10,000 simulations. Based on these aggregated data and assuming independence between events, Bernoulli distribution for event occurrence, exponential distribution of time to outcome, and a 28% relative risk reduction (RRR) with high dose group versus standard dose group, for a two-tailed  $\alpha = 0.05$ , we calculated that the study would have 82.6% power with 1800 patients enrolled (900 per group). This definition of RRR will be a conservative estimate based on a prior meta-analysis suggesting RRR of 48% with the influenza vaccination versus placebo among patients with ACSErro! Fonte de referência não encontrada. and similar to recent IAMI trial a MACE reduction in 28% in ACS patients using influenza vaccine. Of note, although in the IAMI trial the intervention group (in-hospital vaccination after ACS) was compared against placebo, most of the benefit occurred almost

[figure not shown]

immediately, with great separation of event curves within the first 45 days, when the incidence of cardiovascular outcomes is highest. Since we are also comparing the earliness of influenza vaccination, we also expect this magnitude of benefit to be reasonable in our study.

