### 3. STATISTICAL PRINCIPLES

#### 3.1. Confidence intervals and P values

Significance testing will be 2-tailed using  $\alpha = 0.05$ , unless otherwise specified. All analyses and summaries will be produced using R software, version 4.0.3 (or higher), or SAS® version 9.4 (or higher). Confidence intervals, if applicable, were calculated at the 95% nominal confidence level (95% CI).

The primary efficacy outcome will be tested at 5% two-tailed significance level. The second outcomes family were tested following a fixed-sequence method [please, see section 5.4]. A fixed-sequence statistical strategy tests endpoint in a predefined order (see section 5.4), all at the same significance level alpha ( $\alpha = 0.05$ ). If an individual test during any step is not statistically significant, further treatment comparison may continue (i.e., reporting of p-values) but significance will not be claimed, and p-values were deemed as nominally significant.

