## **5.2. Analysis methods**

Primary efficacy outcome: The analysis of primary efficacy endpoint—a hierarchical outcome consisting of all-cause death, MI, stroke, hospitalization for unstable angina, hospitalization for heart failure, urgent coronary revascularization or hospitalization for respiratory infection (excluding COVID-19) will be the comparison between the two arms using the unmatched win ratio method (refer to section 2.3).

Secondary key efficacy outcome: The secondary key outcome is defined also as a hierarchical outcome of CV death, MI, or stroke, in that order, and will be compared with the Win Ratio statistic using the same definitions for the primary endpoint.

Secondary efficacy outcomes: The analysis of the secondary efficacy endpoints, defined as time to first event of: All-cause mortality, Mortality from cardiovascular causes, Myocardial infarction, Stroke, Hospitalization for unstable angina, Need for myocardial revascularization (urgent and non-urgent), Hospitalization for heart failure, TIA (Transient ischemic attack), Hospitalization for respiratory and pulmonary infections, Hospitalization for COVID-19, and Stent thrombosis; will be tested using Cox proportional hazard models. All the effects statistic

[figure not shown]

will be Hazard Ratio (HR) between the two arms within 12 months, and corresponding 95%CI will be provided. Underlying assumptions of the Cox Proportional Hazard Model will be checked using graphical methods

The estimates of time to the first event (median time of event-free) will be also computed if possible, and Kaplan-Meier curves will be displayed, by treatment arm. Additional efficacy outcomes (Influenza season in the southern hemisphere): the prevalence of each strain within of the subtypes circulating in each season and location will be described in tables using proportions and graphically. The proportions will be compared using comparison of proportions tests.

Safety Outcomes: The number of patients having local and systemic adverse events up to 7 days after vaccination will be described by group and overall. The number of patients having any vaccination adverse event will be computed, and the 95% CI will be presented.

All the adverse events will be listed, by patient.

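### The SAP tests an all-pairs win ratio with a binomial formula meant for independent pairs; run as written, the primary test rejects a true null about 94% of the time

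*Combined protocol and SAP*

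**What the plan says.** SAP section 2.3 sets the comparison rule: "every patient from the intervention group will be compared against every patient from the control group". It defines N_w and N_L as the intervention group's total wins and losses over those comparisons, and P_w as N_w / (N_w + N_L). It then says "The p-value will be obtained by the following formula" and prints "z = (P_w - 0.5) / [P_w * (1 - P_w) / (N_w + N_L)]^{1/2}".

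SAP section 5.2 carries this into the primary analysis, "using the unmatched win ratio method (refer to section 2.3"), and gives the key secondary outcome the same definitions. Protocol section 6.2 also compares all patients in one group with all patients in the other.

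On error rate, SAP section 3.1 states: "The primary efficacy outcome will be tested at 5% two-tailed significance level". Section 5.4 puts the primary outcome first in a fixed testing sequence, followed by the key secondary outcome.

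Neither document forms matched pairs or gives a permutation, bootstrap or U-statistic variance. A 95% confidence interval for the win ratio is promised, but no method for it is stated.

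**The concern.** The denominator of the z formula is the standard error of a proportion from N_w + N_L independent trials. That is right when each win or loss comes from its own separate pair of patients. It is wrong when the same patients are reused across pairs. One early death in an arm of 900 produces several hundred losses at once, yet the formula counts each loss as new information. The trial has 1,800 independent units, not a quarter of a million.

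At stake is the meaning of the primary p-value. If the formula is run on all-pairs counts, a win ratio slightly above 1 would be read as superiority and one slightly below 1 as harm. The testing sequence would lose error control at its first step: under the null the primary would nearly always pass, and the key secondary would then meet a test with the same fault.

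**Working it through.** **Inputs.** 900 patients per arm (SAP 2.3), "parallel group and 1:1 allocation trial" (SAP 2.1), two-sided alpha 0.05 (SAP 3.1). Control rates at 12 months (SAP 2.3): death 7.0%, MI 3.4%, stroke 1.0%, unstable angina 2.7%, heart failure hospitalization 2.9%, urgent revascularization 0.6%, respiratory infection 1.0%. Absolute reductions (SAP 2.3): 2.0, 0.9, 0.3, 0.8, 0.8, 0.2 and 0.3 points. Simulation model as in the SAP: independent components, Bernoulli occurrence, exponential times. Complete follow-up is assumed in the main calculation.

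**1. Decided pairs under the null (control rates in both arms).**

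- Probability of no event: q = 0.930 × 0.966 × 0.990 × 0.973 × 0.971 × 0.994 × 0.990 = 0.8269.
- A pair is tied only if neither patient has an event: q² = 0.6838.
- Decided pairs: 900 × 900 × (1 − 0.6838) ≈ 256,162. Simulated mean: 256,165.

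**2. Standard error the SAP formula assumes.** Near the null, SE(log WR) = 2 / √256,162 = 0.00395. The smallest significant P_w is 0.5 + 1.96 × 0.5 / 506.1 = 0.50194, so WR = 0.50194 / 0.49806 = 1.0078.

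**3. Standard error that actually applies.** With complete follow-up the hierarchy ranks all patients from worst to best, with one tied group at the top (no event, share q). A patient's expected net win proportion against a random opponent has mean 0 and variance (1 − q³)/3 = (1 − 0.5654)/3 = 0.1449 under the null. Then:

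- SD of (N_w − N_L)/810,000 = √(2 × 0.1449 / 900) = 0.01794.
- Since log WR ≈ 2(N_w − N_L)/(N_w + N_L), SD(log WR) = 2 × 0.01794 / 0.3162 = 0.1135.
- Valid threshold: exp(1.96 × 0.1135) ≈ 1.25.

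**4. Consequence for the test.** SD of the SAP's z = 0.1135 / 0.00395 ≈ 28.7. Type I error = P(|N(0,1)| > 1.96 / 28.7) = P(|N(0,1)| > 0.068) ≈ 94.6%.

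**5. Simulation, 10,000 trials of 900 v 900.**

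| Scenario | Decided pairs | SAP formula, all pairs | U-statistic test | Finkelstein-Schoenfeld |
|---|---|---|---|---|
| Null, SAP control rates | 256,165 | 94.5% (SD of z 28.5) | 4.6% | 4.7% |
| Null, protocol control rates | 260,809 | 94.7% | 5.2% | 5.3% |
| Null, SAP treated-arm rates | 191,845 | 94.6% | 5.0% | 5.0% |
| SAP rates and reductions | 224,967 | 99.9% | 79.3% | 79.5% |
| Exact 28% relative reduction | 225,332 | 99.9% | 78.5% | 78.6% |
| Protocol rates and reductions | 230,263 | 99.9% | 77.6% | 77.7% |

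The Monte Carlo standard error of the 94.5% is about 0.2 points. Smaller separate simulations under the SAP null (3,000 to 6,000 trials) gave 94.5% to 94.6% for the SAP formula, with 46.7% to 48% of trials falsely favouring the double dose. The Finkelstein-Schoenfeld test rejected 4.5% to 6.0% there; the 6.0% came from the smallest run, where the Monte Carlo standard error is 0.4 points.

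**6. Isolating the cause.** On 900 disjoint, randomly matched pairs (about 285 decided), the same formula rejects 4.8% under the null. The fault therefore lies in applying it to overlapping pairs.

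**7. Robustness.** The documents give no dropout rate. Assuming 10% or 20% loss to follow-up, strong within-patient correlation between events, or both 10% loss and correlation, decided pairs fall to about 204,000 to 232,000 and rejection stays at 93% to 94% (250 trials per scenario).

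**8. The plan's own figures.** Protocol 6.1 gives the target "for a WR of 1.41 with a power of 82.6"%, and SAP 2.3 says "we calculated that the study would have 82.6% power with 1800 patients enrolled (900 per group"). The win ratio reproduces: the simulated median is 1.407. The power does not. The printed formula gives 99.9%, and valid tests give 79.3% to 79.5% with SAP inputs. Treating the components as mutually exclusive gets closer in some versions (84.0% with protocol rates), but contradicts the SAP's stated independence.

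**The case against.** The strongest reply is that the 94% applies only if someone runs the printed formula literally on all-pairs counts. The stated power of 82.6% cannot have come from that formula, which would have shown 99.9%, so the team's simulation code probably used something else, and standard win ratio software would supply a valid variance. The formula is also attributed to a published source.

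Part of this stands. The error rate is a statement about the plan as written, not a prediction of what will be run. But the SAP ties the p-value explicitly to this formula and names only R or SAS, with no package or variance method. Valid tests do not reproduce 82.6% either, so the documents do not show which test was coded. If the analyst departs from the formula, the primary test becomes a choice the plan does not govern. A citation does not make a formula for independent pairs valid on overlapping ones.

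Three limits are fair. The 94.5% counts both directions; the false superiority rate is about half of it. The SAP gives no confidence interval method, so the most that can be said is that an interval built on the same variance would cover about 5% under the null. Under the null the testing sequence would almost always open; it would not open or close at random.

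**Conclusion.** The concern holds. All-pairs comparison and a binomial variance on N_w + N_L cannot both stand. As written, the primary test has a two-sided type I error of about 94.5% instead of 5%, with about 47% of null trials falsely favouring the double dose, and its significance threshold is a win ratio of about 1.008 instead of about 1.25. The key secondary outcome inherits the same test.

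The size rests on the SAP's control rates, 900 patients per arm, independent components and complete follow-up. It changes by no more than about two points under protocol rates, lower event rates, 10% to 20% loss to follow-up or strong within-patient correlation. Separately, power under a valid test is 77.6% to 79.5% depending on which stated inputs are used. That is below the 82.6% claimed and below the 80% level SAP section 2.1 relies on when it accepts 1,800 patients. This must be corrected before the analysis.

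**What to change.** Replace the z formula in SAP section 2.3 with a test whose variance is computed over patients. Either the Finkelstein-Schoenfeld test or a Wald test on log WR with U-statistic variance will do. State the 95% confidence interval method in the same place: the U-statistic variance of log WR, or a patient-level bootstrap. Using the U-statistic variance for both keeps the p-value and interval consistent; if Finkelstein-Schoenfeld is used for the p-value, say which result governs should they disagree at the boundary.

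Apply the same rule to the key secondary outcome, the COVID-19-inclusive sensitivity analysis, the per-protocol and modified per-protocol analyses, and any subgroup analysis that uses the win ratio. Name the software routine. Rerun the power simulation with the chosen test and one agreed set of inputs, since the protocol and SAP differ on control revascularization (1.0% v 0.6%) and on the heart failure reduction (0.7 v 0.8 points), and report the result.

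The cost is one SAP paragraph, standard R or SAS code and a restated power figure. No change to design, sample or data collection is needed. The change should be dated and signed before anyone sees comparative data.

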### Expected event rates in the control arm

|                                                                  |      |
|------------------------------------------------------------------|------|
| Death                                                            | 7.0% |
| Myocardial Infarction                                            | 3.4% |
| Stroke                                                           | 1.0% |
| Unstable angina                                                  | 2.7% |
| Hospitalization for heart failure                                | 2.9% |
| Urgent revascularization                                         | 0.6% |
| Hospitalization for respiratory infection
(Excludes COVID-19) | 1.0% |

### Expected absolute risk reductions for the components of the primary outcome (representing 28% relative risk reduction)

|                                                                  |      |
|------------------------------------------------------------------|------|
| Death                                                            | 2.0% |
| Myocardial Infarction                                            | 0.9% |
| Stroke                                                           | 0.3% |
| Unstable angina                                                  | 0.8% |
| Hospitalization for heart failure                                | 0.8% |
| Urgent revascularization                                         | 0.2% |
| Hospitalization for respiratory infection
(Excludes COVID-19) | 0.3% |

Sample size and power calculation were based on 10,000 simulations. Based on these aggregated data and assuming independence between events, Bernoulli distribution for event occurrence, exponential distribution of time to outcome, and a 28% relative risk reduction (RRR) with high dose group versus standard dose group, for a two-tailed  $\alpha = 0.05$ , we calculated that the study would have 82.6% power with 1800 patients enrolled (900 per group). This definition of RRR will be a conservative estimate based on a prior meta-analysis suggesting RRR of 48% with the influenza vaccination versus placebo among patients with ACSErro! Fonte de referência não encontrada. and similar to recent IAMI trial a MACE reduction in 28% in ACS patients using influenza vaccine. Of note, although in the IAMI trial the intervention group (in-hospital vaccination after ACS) was compared against placebo, most of the benefit occurred almost

[figure not shown]

immediately, with great separation of event curves within the first 45 days, when the incidence of cardiovascular outcomes is highest. Since we are also comparing the earliness of influenza vaccination, we also expect this magnitude of benefit to be reasonable in our study.

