Upon increasing the dose for a higher seroconversion, recent studies have revealed that the high dose vaccine with 60 µg in patients above 65 years old considerably increases immunogenicity against influenza epitopes, reflecting a higher efficacy in reducing respiratory tract infections and also hospitalizations. This increase in elderly population protection may be a prevalent factor in the decrease of hospitalizations and death for different causes, especially those with background cardiovascular disease. In a way that it could be postulated that the increased dose of influenza vaccine (60 µg) could show a potential to reduce cardiovascular events, higher when compared to the standard dose of 15 µg, in this population.

In this sense, an initiative led by *Brigham and Women's Hospital* investigators and financially supported by the US National Institute of Health (NIH), *INVESTED* study, evaluated the effect of the influenza vaccines in increased doses in patients with recent hospitalization for heart failure (last 2 years) or acute myocardial infarction (last year). Based on the above-mentioned idea, this study tested the additional benefits of the use of the 60 µg dose in reducing cardiovascular events in outpatients. As a limitation, it does not propose to test the vaccine during hospitalization, at the most critical moment of the heart disease patient in terms of risk and compliance to the proposed measures. Interestingly, the vaccines used in this trial correspond to an increased trivalent dose versus standard quadrivalent dose vaccine, in a way that the findings could be related to the composition of the vaccine, the vaccine strains or concentration of certain strains in cardiovascular protection, opening a large window to discussion. So that the

recently published results revealed that the study was interrupted early for futility, as after the inclusion of 5260 patients, of the 9200 planned, the DSMB instructed for the interruption as there was no benefit of the intervention with an increased dose of trivalent vaccine (HR 1.06; [95% CI: 0.97-1.17]) in decreasing mortality or cardiopulmonary hospitalization, compared to the quadrivalent standard dose.

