**If the patient is randomized to double dose vaccine, it will be given during the hospitalization for the index event.**

Patients randomized to late standard dose influenza vaccine will receive it at the visit 30 days after randomization.

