## **6. STATISTICAL ANALYSIS**

### **6.1 Sample Size Calculation**

Since the design of the original protocol, the sample size calculation was based on the combined endpoint (MACE) results from a meta-analysis of prospective randomized studies evaluating the effect of influenza vaccines in reducing cardiovascular events after a recent ACS, which revealed a 1-year reduction in relative risk of 36%. The previous version of the protocol considered a conservative event reduction model due

to the use of an active control group, and an event-driven approach, estimating an event rate of 12% per year of the primary endpoint; for a superiority study and a hypothesis of relative risk reduction of 18%, for a statistical power of 90% and a 5% two-sided alpha, 953 events in approximately 9200 patients would be required to complete of the study. However, some facts impacted the VIP-ACS study. With the advent of the COVID-19 pandemic, the number of patients with ACS declined at the investigating sites, and of patients with recruitment potential, most received influenza vaccine with the same strains of the study vaccine, which deemed them ineligible to participate in the study. This fact was relevant as in Brazil the national immunization campaign against influenza was strengthened during the years 2020 and 2021, with the reduction of priority groups and focus on all individuals over 18 years of age.

Another important fact occurred in August 2021, when the IAMI trial results showed that intervention with quadrivalent vaccine versus placebo in patients after ACS provided a 28% reduction in the primary composite endpoint of death from all causes, AMI and stent thrombosis. In addition, pooled data from three previous randomized studies were compiled with IAMI trial data showing a 49% reduction in cardiovascular mortality with influenza vaccine versus placebo, in order to confirm previous findings derived from smaller studies with the same objective.

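### The 28% relative risk reduction is a vaccine-versus-placebo effect applied undiscounted to controls vaccinated at day 30: the sizing is not shown to be conservative, and power is about 79% on the SAP's own inputs and about 40% at an 18% reduction

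*Combined protocol and SAP*

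**What the plan says.** SAP 2.3 assumes a 28% RRR, presented as seven absolute reductions, and reports that "we calculated that the study would have 82.6% power with 1800 patients enrolled (900 per group"). It supports the 28% in two ways. First: "This definition of RRR will be a conservative estimate based on a prior meta-analysis suggesting RRR of 48% with the influenza vaccination versus placebo". Second, it points to a post-infarction trial that found 28% and acknowledges that this trial, too, compared vaccine with placebo. It keeps the figure because most of that benefit appeared within 45 days: "Since we are also comparing the earliness of influenza vaccination, we also expect this magnitude of benefit to be reasonable in our study".

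Protocol 6.1 gives the same power with a win ratio of 1.41 and says the calculation "is comprehensive and conservative to the purpose of the study". Its stated ground there is that the endpoint has more components than those of the cited studies. SAP 2.1 puts power for a 28% RRR above 80%.

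The comparator is set out in Protocol 3.5.2: "Patients randomized to late standard dose influenza vaccine will receive it at the visit 30 days after randomization". Protocol 6.1 also describes the previous version's sizing. The meta-analytic RRR was 36%, a smaller effect was chosen because the control is active, and the calculation was "for a superiority study and a hypothesis of relative risk reduction of 18"%.

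**The concern.** A placebo-controlled effect compares vaccinated patients with patients who stay unvaccinated. Here that contrast lasts only until the control visit at 30 ± 5 days; afterwards both arms are vaccinated and the comparison is double against single dose. Calling 28% conservative because vaccine against placebo gave 48% compares it with the wrong reference. The previous version made an allowance for the active control. The control is still active, the allowance has gone, and the word *conservative* remains.

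What is at stake is how a neutral result would be read. A reader told that power exceeds 80% on a conservative assumption may take a non-significant primary result as good evidence against a worthwhile benefit.

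**Working it through.** **Inputs.** 900 per arm. Two-sided 5% (SAP 3.1: "The primary efficacy outcome will be tested at 5% two-tailed significance level"). Independent Bernoulli events with times drawn separately (SAP 2.3). The 12-month figures, in per cent:

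| Component | Control rate, SAP 2.3 | Absolute reduction, SAP 2.3 | Protocol 6.1, where different |
|---|---|---|---|
| Death | 7.0 | 2.0 | |
| Myocardial infarction | 3.4 | 0.9 | |
| Stroke | 1.0 | 0.3 | |
| Unstable angina | 2.7 | 0.8 | |
| Heart failure | 2.9 | 0.8 | reduction 0.7 |
| Urgent revascularization | 0.6 | 0.2 | control rate 1.0 |
| Respiratory infection | 1.0 | 0.3 | |

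**Test used.** All-pairs hierarchical win ratio with a U-statistic variance for log WR, or the equivalent tie-corrected rank test. The z formula printed in SAP 2.3 was not used. It treats the 900 × 900 = 810,000 pairs as independent and rejected in about 95% of simulations with no effect. That is a separate matter, but it means the formula cannot be the basis of 82.6%.

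**Step 1: the plan's own figure.** The SAP rates and reductions give a median WR of 1.41, which agrees with Protocol 6.1. Simulated power is about 79% (runs from 78.6% to 80.1%, with evenly spread or exponential times). A matched-pairs variant gives 77%, an approximate closed-form variance 74%, and a one-sided 5% test 88%. A uniform 28% on every component gives WR 1.40 and 77–78%. The protocol's rates and reductions give WR 1.39 and 76–78%. No variant tried gives 82.6%.

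**Step 2: a check by hand.** The probability of any event in a control patient is 1 − ∏(1 − pᵢ) = 17.31%. With the SAP reductions it is 12.63%. A two-proportion test at 900 per arm then has 79.4% power, close to the simulation.

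**Step 3: the 18% value.** Multiplying every control rate by 0.82 gives an any-event probability of 14.38%.

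- Difference: 17.31 − 14.38 = 2.93 points.
- Standard error: √[(0.1731 × 0.8269 + 0.1438 × 0.8562)/900] = 0.0172.
- z = 0.0293/0.0172 = 1.70, so power ≈ Φ(1.70 − 1.96) ≈ 40%.
- Simulation: WR about 1.22 and power 38–41%, on SAP or protocol rates.
- Events-based (Schoenfeld) formula: 40.1%.
- Scaling from the plan's own claim: (1.96 + 0.94) × ln 1.225/ln 1.41 = 1.71, so Φ(1.71 − 1.96) ≈ 40%. The answer does not depend on the 3-point gap in Step 1.

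Intermediate values on SAP rates: 25% RRR gives about 68% power, and 20% about 47%.

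**Step 4: was 18% a working figure?** At 12% against 12 × 0.82 = 9.84%, with 90% power, a two-proportion calculation needs 4,380 per arm, or 4,380 × (0.12 + 0.0984) ≈ 957 events. Protocol 6.1 gives 953, so 18% was indeed the effect used.

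**Step 5: what the early-benefit argument requires.** If a share *s* of control events falls early and the early reduction is *r*, with nothing later, the 12-month reduction is *s* × *r*. The documents give neither quantity. As assumptions: *s* = 50% needs *r* = 0.28/0.50 = 56%; *s* = 40% needs *r* = 0.28/0.40 = 70%. Simulated power is about 79% for (50%, 56%), about 70% for (50%, 50%) and about 50% for (40%, 50%).

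**The case against.** The SAP does not hide the comparator. It says the 28% was measured against placebo and gives a reason for keeping it. That stands: the gap is the missing quantification, not disclosure. An effect concentrated early could produce 28% over 12 months, and Step 5 shows that power would then be close to what is claimed.

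The 18% belongs to a superseded, event-driven design with a different composite, set before the post-infarction trial reported. That also stands. It is a sensitivity value, not the plan's current belief or a best estimate.

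Four stronger readings are tempting, and the documents do not support them.

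- *That the early-benefit argument contradicts the exponential model, so that benefit up to day 45 could not exceed 45/365 = 12.3% of events.* This needs a near-constant hazard. The SAP draws occurrence first, gives no exponential rate for timing, and says incidence is highest in the first 45 days.
- *That the SAP assumes 28% up to day 45 and nothing afterwards.* It treats 28% as the overall effect, arising mostly early, which implies an early reduction above 28%.
- *That the cited dose comparison settles the later months.* Protocol section 1 does report that "there was no benefit of the intervention with an increased dose of trivalent vaccine (HR 1.06; [95% CI: 0.97-1.17"), but in outpatients and with a trivalent against a quadrivalent product. The same section cites better protection from higher doses in people over 65.
- *That no non-significant result could exclude an 18% reduction.* With a standard error of log WR near 0.117, an observed WR of 0.97 has an upper limit of 0.97 × exp(1.96 × 0.117) ≈ 1.22. If there were truly no effect, about 37–39% of trials would be non-significant and still exclude 1.22.

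**Conclusion.** The point holds as a correction to the power statement. The documents do not support *conservative*: the 28% and the 48% are both placebo comparisons, and the allowance once made for an active control was dropped without a figure to replace it. On the SAP's own inputs power is about 79%, some 3 to 4 points below 82.6%. At 18% it is about 40%, so like for like it roughly halves.

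These figures assume independent components, the planning rates, complete 12-month follow-up and a valid win-ratio variance. The 40% also assumes the same 18% on every component. The documents do not determine the true effect, so a reader should not conclude that the trial will probably be neutral or that 28% is impossible. The point does not affect the test, the endpoint, the populations or the number enrolled.

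**What to change.** 1. Delete *conservative* from SAP 2.3 and Protocol 6.1, and say there that 28% is a placebo-comparison effect applied to a control arm vaccinated at about day 30.
2. In SAP 2.3, Protocol 6.1 and the synopsis, replace the single 82.6% with re-run power at N = 1800 for 28% RRR, for 18% RRR (labelled as a sensitivity value from the previous design), and for an early-benefit scenario whose early event share and early reduction are stated as assumptions. Name the variance used, and bring the over-80% statement in SAP 2.1 into line.
3. State that a neutral primary result will be interpreted from the planned 95% confidence interval of the win ratio, not from the stated power.
4. In the same edit, reconcile the meta-analytic RRR (36% in Protocol 6.1, 48% in SAP 2.3) and the two differing rate entries in the table above.

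The cost is wording and a re-run of the existing simulation. No patients, data or analyses are added. The downside is a less favourable stated power.
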